## Abstract

**Background:**

Reliable and timely detection of acute rejection in renal transplant patients is important to preserve the allograft function and to prevent premature allograft failure. The current gold standard for the rejection diagnosis is an allograft biopsy which is usually performed upon an unexplained decline in allograft function. Because of the invasiveness of the biopsy, non-invasive tests have been suggested to diagnose acute rejection including mass spectrometry analysis of urine samples.

**Design and methods:**

The aim of this study is to examine the diagnostic accuracy of mass spectrometry analysis in urine for the diagnosis of acute rejections using the biopsy as gold-standard. The study is an ongoing prospective, single-arm, multicentre, phase 3 diagnostic accuracy study. It started in October 2011 and will be concluded in December 2015. Patient within the first year after transplantation who are scheduled for a biopsy to clarify unexplained impairment of the allograft are consecutively recruited into the study. The overall sample size (n = 600) was calculated to demonstrate a sensitivity of 83 % and a specificity of 70 % for a one-sided type one error of 2.5 % and a power of 80 % per hypothesis. Biopsy evaluation and mass spectrometry analysis of urine samples (obtained immediately before biopsy) are performed independently by different readers without knowledge from the respective other assessment. The follow-up observation period is 6 months. For the primary analysis, the lower limits of the two-sided 95 % Wald confidence intervals for sensitivity and specificity will be compared with the pre-specified thresholds (83 % for sensitivity and 70 % for specificity). In secondary analyses the predictive values, the diagnostic measures in subgroups, and the clinical course will be assessed.

**Discussion:**

Previous phase 2 diagnostic accuracy studies (in small selected study populations) provided sufficient evidence to suggest mass spectrometry on urine samples as a promising approach to detect acute rejections. This study determines the diagnostic performance of the test in the routine setting of post-transplant patient care, compared to the biopsy-based rejection diagnosis. The next step would be a randomized trial to compare the two diagnostic strategies (including the urine test or not) in relation to patient relevant endpoints.

**Trial registration:**

NCT01315067; March 14, 2011

**Electronic supplementary material:**

The online version of this article (doi:10.1186/s12882-015-0146-x) contains supplementary material, which is available to authorized users.

## Background

Acute rejection is an important factor that determines the long-term function and survival of the renal allograft. Therefore, timely detection and appropriate treatment of acute rejections is an important objective in the post-transplant care. Approximately 15-30 % of the transplanted patients suffer from one or multiple episodes of acute rejection which occur mainly in the first year of transplantation [1]. The most common type of acute rejection − with more than 90 % − is the T-cell mediated tubulointerstitial rejection (Ia and Ib according to BANFF classification). Acute T-cell mediated vascular rejection and acute humoral rejection are less frequent in the first transplant year [2, 3].

The detection of acute rejection in an early stage is challenging [4]. The current standard in the allograft surveillance relies on regular monitoring for increases in serum creatinine or a decrease in creatinine clearance which then triggers subsequent biopsy. This implies that acute rejections are diagnosed at a stage where the morphological damage already has led to a relevant functional impairment of the graft. Because of this problem some transplant centres perform protocol biopsies as part of the post-transplant care which can detect acute rejections at an early subclinical stage before functional impairment has occurred. However, biopsies are invasive and even with frequent regular protocol biopsies rejection episodes may be missed.

Therefore, many attempts have been made to develop non-invasive tests in blood or urine which are able to detect acute rejection. Most of these approaches used single markers or combinations of a few markers. Mostly due to lacking specificity and sensitivity of these markers, none of these tests are established in the clinical routine and post-transplant care of the patients [4]. An alternative approach, which takes in account the heterogeneity of the rejection process, is the use of multiple markers as detected by mass spectrometry in urinary samples.

A few diagnostic phase 1 and phase 2 studies with such non-invasive blood and urine tests (according to [5, 6]) demonstrated promising results regarding sensitivity and specificity for the diagnosis of rejection [7–12]. However, until now the validation of these approaches in a representative study population and in the clinical routine of the post-transplant is still missing thus prohibiting a realistic estimation of sensitivity and specificity of these tests.

Beside the small sample sizes in these studies there are some further limitations. The histological scoring among the different studies is not uniformly conducted according to the BANFF classification [7, 9]. Partially, histological confirmation of the absence of rejection in the test-negative patients is missing (leading to the so called differential verification bias). Another important limitation is that, due to the small sample sizes, effects of potential confounders, like infectious conditions or different immunosuppressive regimens, are unknown.

Extending our proof-of concept study on 26 patients with acute tubulointerstitial rejection [10], we started out to refine and standardize the sample processing and analysis [13]. The resulting peptide pattern was validated in a cohort of 25 patients with and 43 patients without rejection. The AUC value was calculated to be 0.89 (95 % CI: 0.80 – 0.95). In a replication with a blinded test set of 17 independent patients, 6 of 7 patients with acute rejection were correctly classified as having rejection and 10 of 11 samples were correctly classified as negative for rejection (AUC: 0.83; 95 % CI: 0.57-0.96).

Moreover, we were able to identify the sequences of four peptides of the rejection pattern and found that three are fragments of the collagen type I alpha(I) (Col1A1) whereas the other is collagen type I alpha(III) derived. Similar results with changes of Col1A1 fragments in acute renal allograft rejection have been reported very recently [12]. In our peptide pattern, two of the Col1A1 fragments were less abundant in the rejection samples and one was increased. Aligning these fragments to other, commonly found Col1A1 peptides in the urine samples, we found that the increased peptide (ID-114633) possess a PGP motif at the c-terminal end which is indicative of increased matrix degradation by MMP-8 and MMP-9. Double-stains of the biopsies for MMP-8 and for an endothelial cell marker revealed confinement of MMP-8 to polymorphonuclear leukocytes located within pertubular capillaries and sparsely, in the interstitial infiltrates and glomerular capillaries of biopsies with rejection [13].

Given all these facts, sufficient evidence exists to suggest mass spectrometry on urine samples as a promising approach to detect acute rejection. However, proof is lacking that this test provides good diagnostic performance in the routine setting of the post-transplant patient care, compared to the biopsy-based rejection diagnosis.

Therefore, the aim of this multicentre prospective phase 3 diagnostic accuracy study is to investigate if the mass spectrometry (MS) test developed by Metzger et al. [13], is useful in a representative setting of the clinical routine post-transplant care. Meticulous collection of clinical data including potential confounders and use of rigorous histological standards (BANFF classification, repeat central pathology reading of biopsies) in this trial will maximize the interpretation of the obtained mass spectrometric results. At the end, reliable estimators of the diagnostic accuracy (sensitivity, specificity, predictive value, limits of the test) will be derived from the trial.

## Methods/Design

### Study aims and objectives

The aim of the study is to prove that the MS test has good diagnostic performance compared to the allograft biopsy to detect acute tubulointerstitial rejection in renal-transplant patients who undergo a biopsy for unexplained renal dysfunction.

The primary objective of the trial is to show that mass spectrometry is not relevantly inferior to the gold-standard allograft biopsy regarding sensitivity and specificity.

The secondary objectives are to evaluate the predictive values of the MS test and to investigate the diagnostic accuracy of the MS test in subgroups, namely in patients with different histological severity of the rejection, with different severity of functional impairment, with kidney versus a combined kidney/pancreas transplant, with potential confounders present (e.g. urinary tract infection, concurrent CMV infection, polyomavirus nephropathy), and in patients from different study centres.

### Study design

This study is a prospective multicentre phase 3 diagnostic accuracy study (according to [5, 6]) for the intra-individual comparison of the MS test and the allograft biopsy. The MS test is the index test, while the allograft biopsy is the gold standard. Biopsy and mass spectrometry will be performed independently by different readers without knowledge from the respective other assessment. Results of the MS test will be kept concealed until the end of the study. Accordingly, this is a non-interventional trial because the treatment is guided by the result of the allograft biopsy, as the current diagnostic standard. All treatments are permitted which are deemed necessary by the clinicians caring for the patients.

### Study setting and period

This study is carried out in 10 German university and non-university transplant centres: Hannover, Aachen, Jena, Erlangen, Freiburg, Essen, München, Köln, Berlin, Hannoversch Münden. It is expected that virtually all patients who are scheduled for an indicated biopsy agree to participate in the study because of the non-interventional nature of the trial. Drop-out rate will be negligible for primary analysis because once a patient has consented to participate in the study the essential data set is available for analysis.

Data collection was initiated in October 2011 and the conclusion of this study is scheduled for December 2015.

### Participants/eligibility criteria

The test should be applicable to all kidney or kidney/pancreas transplant patients in the post-transplant care which are scheduled for an indicated biopsy to verify clinical symptoms of an acute rejection. Therefore, inclusion/exclusion criteria are set out to the least limitations that are necessary to perform the study meaningfully, i.e. availability of the results of the comparator ‘renal allograft biopsy’. The inclusion of patients within the first year of transplantation is based on the fact that acute rejections are most frequent in this period. Thus, this population is suitable for estimation of sensitivity and specificity with high accuracy. Furthermore for this population the test would have the greatest relevance.

The inclusion criteria imply that female and male patients are likewise studied. As this study is carried out in the setting of adult renal allograft recipient post-transplant care, results will be applicable to all adult patients. Enrolment to the study is only allowed once for each patient, i.e. patients with repeated episodes of suspected acute rejection are not included a second time.

### Recruitment, procedures and follow-up

After identification of a patient with unexplained allograft function decline (within the first year after transplantation) and the clinical decision to perform a biopsy, informed consent is obtained from the patient to use an urine sample from the day of biopsy and the clinical data for the study.

The urine specimen is obtained immediately before the biopsy as a spot sample. Mass spectrometry is performed on this sample, along with the usual clinical routine determinations (protein concentration and sediment analysis).

The follow-up observation period after acquisition of the sample is 6 months. Main parameters to be used from the follow-up period are changes in renal allograft function (calculated GFR at 6 months after the biopsy in relation to the GFR before and at the time of biopsy) and further acute rejection episodes. For the assessment of allograft function 6 months after inclusion in the study, a regular out-patient visit will be scheduled for this time point. If the follow-up visit is impossible, all efforts will be made to obtain the necessary information from the primary care physician of the patient.

For the illustration of the trial flow see Fig. 1.

**Fig. 1 Fig1:**
[figure not shown]
Trial flow (including pre-study steps)

### Index test

The index test uses CE-MS technology. Compared with other spectrometric and spectroscopic technologies, i.e., SELDI, NMR, the CE-MS technology offers a wider and more adjustable measurement range which is particularly suited for peptides and small proteins of approximately 9 to 180 amino acids in length. Thus, this technology is more sensitive for the detection of peptides in complex sample matrices (~1 fmol). It facilitates a higher degree of throughput (<1 h per sample) and automation (on-line coupling of CE and MS data acquisition via contact-close relays).

For the index test ‘acute rejection diagnosis by CE-MS’ neither internationally accepted pre-defined peptides for the rejection diagnosis, nor units, cut-offs or categories are available.

Classification of patient samples with the rejection pattern is expressed as membership probability and quantified by the Euclidean distance of the data point to the maximal margin of a separation hyperplane between cases and controls in a multidimensional space constructed by the peptide classifiers (by the use of Support Vector Machines, SVM). Membership probability therefore expresses the degree of similarity of a patients’ peptide profile to the one that was identified to be specific for the disease in the discovery phase on histomorphologically well-defined patients.

Test results of the samples will be classified into the categories ‘rejection’ and ‘no rejection’ by the pre-specified urinary peptide patterns and algorithms at the cut-off point of −0.25 based on the evaluation of CE-MS profiles of patients included in the proof-of-concept study.

### Standard of truth

The true disease state is assessed by biopsy according to the established BANFF criteria because this is the only accepted standard of truth for acute rejection diagnosis. This standard of truth is used throughout all relevant clinical trials and in the clinical routine to diagnose or to rule out acute rejection in renal transplant patients [14].

It is conceivable that the mass spectrometry test may detect acute rejections that are missed by biopsy because of the focal nature of the rejection in the allograft or because of potential biopsy sampling errors. Therefore, a sensitivity analysis will be performed secondarily for the cases with a positive mass spectrometry result and a negative biopsy, by using the clinical course and subsequently performed biopsies (if available) for an assessment of the probable true disease state at the time of first diagnosis.

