### Statistical issues

#### Sample size

The primary objective of the trial is to show that mass spectrometry is not relevantly inferior to the gold-standard allograft biopsy. The null hypothesis of the study is that sensitivity and specificity of mass spectrometry are relevantly reduced compared to the gold standard biopsy. Thresholds are set to 83 % for sensitivity and to 70 % for specificity. Sample size calculation was done with nQuery 4.0, separately for sensitivity and specificity. The pre-test probability of acute rejection in kidney or kidney/pancreas transplanted patients with indication biopsy is expected to be 25 % (Hannover Transplant Centre Data; unpublished). The estimators of the test set of the previous phase II study are 91 % for sensitivity and 76 % for specificity. For both sample size calculations a one-sided χ^2^-test for single-proportion is used, assuming a one-sided type one error of 2.5 % and setting the power to 80 %. For a sensitivity of 83 % under the assumption of a true sensitivity of 91 %, 150 patients with acute rejection are needed, for a specificity of 70 % under the assumption of a true specificity of 76 %, 440 patients without acute rejection are needed. So, assuming the pre-test probability of 25 %, in sum a total sample size of 600 patients should be sufficient, where the patients with acute rejection (150 as 25 % of 600) determine the overall required number of patients.

No adjustment for multiplicity is necessary for testing sensitivity and specificity because both hypotheses have to be rejected, if the study should be evaluated as success. Loss to follow-up will not affect the analysis of primary and secondary outcomes because all necessary data for these calculations are collected at the time of urine sampling and renal biopsy on day 1 of the study.

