#### Statistical analysis

For the primary analysis, point estimators and two-sided 95 % Wald confidence intervals for sensitivity and specificity will be calculated. The null hypothesis for sensitivity will be rejected if the lower bound of the corresponding confidence interval is above 83 %. The null hypothesis for specificity will be rejected if the lower bound of the corresponding confidence interval is above 70 %.

For the key secondary analyses, predictive values for all patients and sensitivity, specificity and predictive values for subgroups will be analysed descriptively. Subgroups are: patients with different BANFF grades of acute rejection; patients with different severity of acute rejection in terms of functional impairment at the time of rejection; patients with kidney allografts alone and patients with combined kidney/pancreas transplantation; patients from each transplant centre; patients with concurrent urinary tract infection at the time of biopsy/urine sampling; patients with concurrent CMV infection at the time of biopsy/urine sampling and patients with polyomavirus nephropathy.

Furthermore, the secondary analysis examines whether certain clinical, laboratory or pathological variables interfere with the mass spectrometric test. This facilitates the search for potential confounders and the definition of the limits of the MS test.

For the primary analysis no missing data due to drop-outs is expected because once a patient has consented to participate in the study the data for primary analysis is available. Drop-outs would only affect analysis of follow-up data (e.g. rejection events after the test).

Within the sensitivity analysis, the clinical course and subsequently performed biopsies (if available) will be additionally used for an assessment of the probable true disease state in case of a positive mass spectrometry result and a negative biopsy. Also, the results of the central read of the biopsy vs. the local pathological diagnosis will be used in the sensitivity analysis.

In a descriptive secondary analysis, the test reproducibility will be evaluated. Therefore, Krippendorff’s alpha will be calculated for the probe pairs (of 10 % of the patients).

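### The secondary sensitivity analysis for rejections missed by biopsy reassesses only MS-positive/biopsy-negative patients, so recomputed sensitivity and specificity cannot fall

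*Protocol article*

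**What the plan says.** The protocol article describes the reassessment twice, with the same scope. Under Standard of truth, "a sensitivity analysis will be performed secondarily for the cases with a positive mass spectrometry result and a negative biopsy". Under Statistical analysis, clinical course and later biopsies serve for an "assessment of the probable true disease state in case of a positive mass spectrometry result and a negative biopsy". The reason given is that the "mass spectrometry test may detect acute rejections that are missed by biopsy because of the focal nature of the rejection", or because of sampling error.

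A second component is planned: "the results of the central read of the biopsy vs. the local pathological diagnosis will be used in the sensitivity analysis". It is not restricted by MS result.

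The primary analysis uses the biopsy and urine sample of day 1. Under Sample size, "Thresholds are set to 83 % for sensitivity and to 70 % for specificity". Follow-up of 6 months, covering GFR change and further rejection episodes, is planned for all patients (Recruitment, procedures and follow-up). MS results stay concealed until the end of the study (Study design).

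**The concern.** Focal rejection and needle sampling error arise in the tissue. They can produce a falsely negative biopsy in a patient with a negative urine test as well as in one with a positive test. In an MS-positive patient, finding the missed rejection turns an apparent false positive into a true positive, which favours the test. In an MS-negative patient it reveals a hidden false negative, which counts against the test. The plan looks only in the first group.

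If accuracy is recalculated after that step, the result is fixed in direction before any data are seen. A reader would take it as evidence that the accuracy estimates withstand an imperfect biopsy, when the analysis could not have shown otherwise. The central re-read does not fill the gap: it looks again at the same tissue and cannot find rejection that the needle missed.

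**Working it through.** **Inputs, all from Sample size.** 600 patients and 25% prevalence, so P = 150 biopsy-positive and N = 450 biopsy-negative; assumed sensitivity 91% and specificity 76%; thresholds 83% and 70%; one-sided 2.5% error and 80% power.

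**The plan's own figures.** With n = [1.960·√(p0·q0) + 0.842·√(p1·q1)]² / (p1 − p0)²:
- sensitivity, 0.83 against 0.91: 149.17, rounded up to 150;
- specificity, 0.70 against 0.76: 439.33, rounded up to 440;
- total: 150/0.25 = 600.

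All three match the plan.

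**Planned table.** TP = 0.91 × 150 = 136.5; FN = 13.5; TN = 0.76 × 450 = 342; FP = 108.

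**Direction.** Moving k patients from FP to TP gives Se(k) = (TP + k)/(P + k) and Sp(k) = TN/(N − k). The changes are
- Se(k) − Se(0) = k·FN/[P(P + k)] ≥ 0;
- Sp(k) − Sp(0) = k·TN/[N(N − k)] ≥ 0.

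Neither depends on whether the test is any good. A numerical check of 626,145 combinations of table and k found no decrease. Even an uninformative test at 50%/50% (FP = 225) rises to 97.5/172.5 = 56.5% and 225/427.5 = 52.6% when 10% of its false positives are moved.

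**Size of the one-sided shift.** The share of false positives reclassified is not in the document, so a range is shown.

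| Share of the 108 moved | Sensitivity | Specificity |
|---|---|---|
| 0% | 91.0% | 76.0% |
| 10% (k = 10.8) | 147.3/160.8 = 91.6% | 342/439.2 = 77.9% |
| 20% (k = 21.6) | 92.1% | 79.8% |
| 30% (k = 32.4) | 92.6% | 81.9% |
| 50% (k = 54) | 93.4% | 86.4% |

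**What a two-sided reassessment could show.** Hold 10.8 missed rejections in the MS-positive group and let d be the share of all missed rejections that MS detects. The total missed is 10.8/d, of which 10.8/d − 10.8 lie among MS-negative patients. Then Se = 147.3/(150 + 10.8/d) and Sp = [342 − (10.8/d − 10.8)]/(450 − 10.8/d).

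| d (assumed) | Missed in total | Of these MS-negative | Sensitivity | Specificity |
|---|---|---|---|---|
| 91%, as for biopsy-proven rejection | 11.9 | 1.1 | 147.3/161.9 = 91.0% | 340.9/438.1 = 77.8% |
| 50% | 21.6 | 10.8 | 147.3/171.6 = 85.8% | 331.2/428.4 = 77.3% |
| 24%, chance share (108/450) | 45.0 | 34.2 | 147.3/195 = 75.5% | 307.8/405 = 76.0% |

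The one-sided analysis reports 91.6%/77.9% in all three rows.

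**The case against.** Four stronger readings are tempting, and the document does not support them.

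- *A failed trial could be turned into a success.* Success requires both Wald lower limits to exceed their thresholds in the primary analysis, which rests on day-1 data. The reassessment is secondary and carries no threshold or decision rule. Applying the primary criterion to a reclassified table would be the reader's construction.
- *The plan repeats the flaw it criticises.* The Background faults earlier studies because "histological confirmation of the absence of rejection in the test-negative patients is missing (leading to the so called differential verification bias". Here every patient is biopsied and the primary analysis has no differential verification. Reassessing by index result in a secondary analysis is a related but lesser problem.
- *True sensitivity would be 75.5% rather than 91.6%.* That needs MS to carry no information about missed rejections while detecting 91% of proven ones. If it detects missed rejections equally well, the gap is only 0.6 points.
- *The assessor is necessarily unblinded.* An assessor given only these patients could infer the MS result, but the article does not say how cases will be presented. That is a detail for the analysis plan.

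Two further points stand in part. The text describes only an assessment of the probable disease state and does not say that accuracy will be recomputed; calling it a sensitivity analysis suggests so, but does not settle it. The central-versus-local reading can move estimates either way, so checking of the reference standard as a whole is not one-directional.

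What remains is that the population for reassessment is stated, twice, and its restriction does not follow from the reason given.

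**Conclusion.** The point holds for the reassessment by clinical course and later biopsies, on the condition that sensitivity and specificity are recomputed from it. Under that condition neither measure can fall. Strictly, they can also stay unchanged: both if nobody is reclassified, and sensitivity alone if there are no false negatives. The analysis therefore cannot test robustness to missed rejections in both directions.

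The practical size depends on how well MS detects rejections that the biopsy misses, which is unknown. With 10% of false positives reclassified, the one-sided sensitivity exceeds the two-sided one by 0.6 points (91.6 − 91.0), 5.8 points (91.6 − 85.8) or 16.1 points (91.6 − 75.5) for detection of 91%, 50% or 24%. The 10% and the detection rates are assumptions. This should be fixed, but it does not threaten the co-primary result.

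**What to change.** Apply one pre-specified follow-up rule to all biopsy-negative patients regardless of MS result. It should draw on the planned data: further rejection episodes, change in GFR at 6 months, and later biopsies where available. Assessors should be blinded to MS and finish before MS results are released; since these are concealed until study end, this fits the existing design. Recompute sensitivity and specificity from the full reclassified table.

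If that is not done, report the MS-positive-only reassessment purely as a description of apparent false positives, and not as an estimate of accuracy.

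The cost is a change of wording and, at planning values, review of about 342 more records (the MS-negative/biopsy-negative patients). No new procedures are needed. Some of these patients will have incomplete follow-up or no later biopsy, and the numbers should be reported by MS result.
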